### Sample size calculations

Data from the systematic review of CTG + FBS trials and observational data from Australian hospitals support a conservative estimate of up to a 40 % relative risk reduction in caesarean sections when FBS is added to CTG monitoring [12, 27, 28]. Based on a conservative 35 % relative reduction in Caesarean Section, from 38 % of women who exhibit a non-reassuring CTG during labour to 25 %, a sample size rounded up to 300 in each group is required (total 600, alpha 0.049 (to allow for one interim analysis), power 90 %). The trial would also have 92 % power to detect a 25 % reduction in combined operative births (caesarean + vacuum + forceps) from 55 % to 41 % [12].

### Compliance

Compliance with the protocol for the trial study groups will be audited by hospital record review of actual attempts to take FBS for lactate estimation in each group. Barriers to compliance will be identified and, where possible, addressed as soon as practical during the trial.

### Feasibility

The Royal Women’s Hospital is the largest tertiary maternity centre in Victoria, Australia, with over 7000 births annually. The investigator team includes the Head of the University Department of Obstetrics and Gynaecology, Neonatologists, maternity team leaders, the Medical and Midwifery Directors of Birth Suite and clinical researchers experienced in the evaluation of techniques for fetal welfare assessment. Several members of the investigator team co-authored the hospital’s Clinical Practice Guidelines for fetal scalp blood sampling in labour.

Two of the investigators ([name] and [name]) have previously conducted an RCT of intrapartum fetal oximetry, which was (i) a novel technology that required considerable clinician expertise; and (ii) was not standard care. These factors were noted as barriers to recruitment, as was the challenge of timing of approach when women were in labour. Despite these barriers, we successfully recruited the full sample of 600 in 3.5 years.

### Analysis

The consultant statistician for the interim analysis will present data to the data monitoring committee in unlabelled study groups. The data management team will remain blinded to group allocation until the final analysis. Analysis will be by intention to treat and all randomised subjects will be included. Demographic information will be summarised for the groups using descriptive statistics, to ensure the groups are comparable. Proportions will be compared by Chi-squared analysis, risk ratios and their 95 % confidence intervals. Continuous variables will be compared by t-tests or their non-parametric equivalent. Logistic regression will compare the between-group difference in caesarean section. Time to event data will be analysed by Kaplan-Meier statistics. Women’s scores from the maternal perceptions questionnaire will be compared for the two groups using Wilcoxon signed rank test.

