### Randomisation and group allocation

A researcher not otherwise involved with the trial will use computerised sequence generation with permuted block randomisation, stratified for parity (nulliparous, parous), to develop the randomisation sequence that will be applied through sequentially numbered, sealed, opaque envelopes. Those women whose CTGs meet the inclusion criteria will be randomised in a 1:1 ratio to the CTG-only group or the CTG + lactate group. Clinical care during labour and birth will continue with the woman’s obstetric and midwifery team. Neonatal care will be the provided by the neonatal team, according to national resuscitation guidelines.

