#### Secondary study endpoints

Maternal endpoints, identified in the Cochrane systematic review [2]:Total operative birth (forceps + vacuum + caesarean section)Total operative vaginal birth (forceps + vacuum)Normal vaginal birthCaesarean section specifically for the indication of non-reassuring fetal statusAssisted vaginal birth (forceps or vacuum) for non-reassuring fetal statusMaternal satisfaction with fetal monitoring in labourMaternal length of hospital stayFetal/neonatal endpointsThe fetal oximetry trial [50] demonstrated equivalence in fetal and neonatal outcomes when comparing the use of CTG with fetal oximetry added to CTG. This is relevant, because although poor outcomes resulting from hypoxia are rare, they are important. For this reason, our team of investigators includes experienced neonatologists. Based on recommendations for definitions of serious outcomes by the Australian New Zealand Neonatal Network and expert recommendation for important measures of morbidity at and beyond term [56, 57], we will record:Composite fetal/neonatal endpoint: Death or serious outcome for the infant: includes one or more of fetal death after trial entry; death of a liveborn infant prior to hospital discharge; neonatal encephalopathy (stages II/III) [58]; Apgar score <4 at 5 min; care in neonatal intensive care unit >96 h.Other neonatal morbidity outcomes will include: individual components of the composite fetal/neonatal outcome; neonatal encephalopathy (stages I, II, III) [58]; Apgar score <7 at 5 min; umbilical cord arterial and venous and first neonatal blood gas (within two hours of birth) pH, base deficit and lactate; resuscitation by bag and mask ventilation, intubation, external cardiac massage and/or adrenaline; admission to neonatal intensive care; neonatal length of hospital stay.Economic: Cost-effectiveness of fetal monitoringConsiderations related to fetal scalp blood lactate measurement only: We will also record the success rate of fetal scalp blood sampling for fetal lactate and fetal scalp laceration or infection requiring treatment.

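### For the rarest serious infant outcomes, the only effect measure named is the risk ratio, which at 300 per arm may be undefined or practically unbounded; a risk difference should be added.

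*Protocol article*

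**What the plan says.** Under Analysis, the protocol article states: "Proportions will be compared by Chi-squared analysis, risk ratios and their 95 % confidence intervals". One further model for a binary outcome follows, for the primary endpoint alone: "Logistic regression will compare the between-group difference in caesarean section". The method for the risk-ratio interval is not named.

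Under Secondary study endpoints, the article explains why infant outcomes are collected: "although poor outcomes resulting from hypoxia are rare, they are important". It pools five serious outcomes into a composite: fetal death after entry, death before discharge, stage II/III encephalopathy, a 5-minute Apgar score below 4, and more than 96 hours of neonatal intensive care. Among the further morbidity outcomes it then lists "individual components of the composite fetal/neonatal outcome". No expected rate is given for the composite or for any component.

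The sample size section plans 300 women per group, and the randomisation section allocates them 1:1.

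**The concern.** The article itself expects these infant outcomes to be rare, yet the measure it names for them is a ratio of two small counts. If the CTG-only arm has no events, the ratio is infinite. If the lactate arm has none, it is 0. If neither has any, it is 0/0. This is a question about a stated choice of measure, not only about a detail left unsaid.

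At stake is the safety half of the conclusion. The Discussion hopes for fewer caesarean sections with no cost to the baby. For a rare outcome, that hope is supported by an upper limit on the absolute excess of harm, such as extra cases per 100 births. A ratio whose upper limit is infinite, or which does not exist, supplies no such limit, even though the same counts can.

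**Working it through.** **The plan's own figure.** The sample size section says "a sample size rounded up to 300 in each group is required (total 600, alpha 0.049 (to allow for one interim analysis), power 90" %, for caesarean section "from 38 % of women who exhibit a non-reassuring CTG during labour to 25" %. The usual two-proportion formula, two-sided (an assumption, as sidedness is not stated), gives 268 per group, or 283 with a continuity correction. Both round up to 300, and 300 per group gives 93% power. For operative birth (55% v 41%) the power is also 93%, against 92% stated. So n = 300 per arm is sound for the common outcomes and is used below.

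**Inputs for the rare outcomes.** n = 300 per arm comes from the protocol. The true event rate p is not in the documents; it is assumed equal in both arms and varied from 0.1% to 2%.

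**Chance of empty arms.**
- One given arm empty: (1 − p)^300
- At least one arm empty: 2(1 − p)^300 − (1 − p)^600
- Both arms empty: (1 − p)^600

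| Assumed rate | Expected events per arm | At least one arm empty | Both arms empty |
|---|---|---|---|
| 0.1% | 0.3 | 93% | 55% |
| 0.25% | 0.75 | 72% | 22% |
| 0.5% | 1.5 | 40% | 5% |
| 1% | 3 | 10% | 0.2% |
| 2% | 6 | 0.5% | <0.1% |

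Example at 0.25%: 0.9975^300 = 0.472 and 0.9975^600 = 0.223, so 2 × 0.472 − 0.223 = 0.721. Setting the middle formula equal to 0.5 gives p = 0.41%.

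**What each measure yields (lactate v CTG-only, 300 each).** The risk-ratio column gives the score interval, which is more favourable to the plan than the ordinary log interval, since the latter does not exist with an empty arm.

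| Events | Risk ratio, score 95% CI | Risk difference, Newcombe 95% CI |
|---|---|---|
| 0 v 0 | undefined | 0.0% (-1.3% to +1.3%) |
| 3 v 0 | infinite (about 0.78 to infinity) | +1.0% (-0.4% to +2.9%) |
| 0 v 3 | 0 (0 to about 1.27) | -1.0% (-2.9% to +0.4%) |
| 0 v 1 | 0 (0 to about 3.8) | -0.3% (-1.9% to +1.0%) |

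The Newcombe limits come from the Wilson limits of each arm: 0/300 gives 0 to 1.26%, and 3/300 gives 0.34% to 2.90%. For 3 v 0:
- lower limit = 1.0% − √[(1.0 − 0.34)² + 1.26²]% = 1.0% − 1.42% = -0.4%
- upper limit = 1.0% + (2.90 − 1.0)% = +2.9%

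Adding 0.5 to each cell for 3 v 0 gives a risk ratio of 7.0 (0.36 to 135). That is finite, but no practical bound.

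**Does the test fail too?** The exact size of the uncorrected chi-squared test at nominal 5%, summed over all tables with 300 per arm and counting an empty table as no rejection, is 0.04% at a rate of 0.1%, 3.0% at 0.5%, 4.6% at 1%, 4.9% at 2% and 5.1% at 3%. It is conservative when events are very few and does not materially exceed its level. The weakness is in the effect measure.

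**The case against.** The strongest reply is that this is one paragraph of a journal article. The interval method and the handling of sparse tables are commonly left to the full protocol or the SAP, which are not shown. That stands as far as the interval method goes, and no fault is found there. It does not dispose of the point, because the choice of the risk ratio is stated, and an analysis plan that follows the sentence literally would carry it over.

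A reader might infer more than the documents support:

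- *The risk ratio is the only effect measure for any proportion.* It is not: logistic regression is also planned for caesarean section.
- *An empty arm leaves no interval.* That is true of the ordinary log interval, which the article does not specify. Score or 0.5-corrected intervals exist with one empty arm; only 0 v 0 is truly undefined. When the lactate arm is the empty one, the score interval even has a finite upper limit, though with a single event in the other arm it is about 3.8.
- *The infant outcomes will often have no estimate at all.* This depends on rates the article does not give. Both arms are empty more than half the time only at about 0.1%.
- *The safety result as a whole is lost.* The composite pools five outcomes, and one of them, prolonged intensive care, need not be rare. At 1% or more an empty arm has less than a 10% chance.
- *The chi-squared p-values are invalid.* The test holds its level at or near 5% over the assumed range.

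It is also fair to say that if counts per arm are published, anyone can compute a risk difference later.

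**Conclusion.** The point holds in a limited form. For very rare single components of the infant composite, the named measure is likely to give 0, infinity or no value. Where the CTG-only arm is the empty one, the interval has no usable upper limit on harm. The threshold is an assumed rate of about 0.4% per arm; below it, an empty arm is more likely than not. This rests on 300 analysed babies per arm, equal true rates, and a rate that must be assumed because the protocol gives none. The composite at 1% or more is seldom affected, and caesarean section and operative birth are not affected. Nothing here questions the sample size or the primary analysis. This is an inexpensive improvement to the safety reporting rather than a flaw in the design.

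**What to change.** Add one sentence to the Analysis section or the SAP. For the fetal/neonatal composite, each of its components and any other binary outcome with few events, report the counts per arm and the risk difference with a score-based 95% confidence interval (Newcombe or Miettinen-Nurminen) alongside the risk ratio; give the risk ratio only where it can be estimated. Newcombe's interval has the practical advantage of a closed form that works directly for 0 v 0. An exact p-value is optional.

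The cost is that sentence and slightly more analysis. No new data are needed, and the sample size and primary analysis do not change. The sentence should be fixed before the data are unblinded, so that the choice of measure cannot depend on which arm turns out to be empty.

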### Study endpoints

#### Primary study endpoint: caesarean section

The Cochrane systematic review of lactate measurement in labour identified the caesarean section rate as a key endpoint for the evaluation of this form of fetal welfare assessment [2].

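### Randomisation is stratified by parity, but the chi-squared test and risk ratio carry no parity term, and the Analysis section does not say which analysis of caesarean section is primary

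*Protocol article*

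**What the plan says.** Under Randomisation and group allocation, the protocol article specifies "permuted block randomisation, stratified for parity (nulliparous, parous"), with women "randomised in a 1:1 ratio to the CTG-only group or the CTG + lactate group". Parity is the only stratification factor named.

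The endpoint heading reads "Primary study endpoint: caesarean section". The effect is framed as proportions and a relative reduction: Sample size calculations goes "from 38 % of women who exhibit a non-reassuring CTG during labour to 25" %, described as a 35% relative reduction, with "total 600, alpha 0.049 (to allow for one interim analysis), power 90" %.

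Two sentences of the Analysis section apply to this endpoint. The general one says "Proportions will be compared by Chi-squared analysis, risk ratios and their" 95% confidence intervals. The specific one says "Logistic regression will compare the between-group difference in caesarean section". Parity is not mentioned in that section. No covariates are listed for the logistic model, no effect measure is named for it, and neither analysis is called primary.

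**The concern.** Stratified blocks force the arms to be nearly balanced on parity. The true sampling variance of the treatment comparison then contains only the variation within parity strata. An unstratified chi-squared test and a crude risk ratio use the total variance, which also includes the variation between strata. If parity predicts caesarean section, their standard errors are too large: the test rejects less often than its nominal level, and precision bought by stratifying is not used.

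The second issue is which result counts. Caesarean section is a proportion and is also the endpoint named for logistic regression, so two analyses apply with no ranking. If the logistic model includes parity, it is a different test from the chi-squared, and the two could disagree near 0.049. If it does not, the p-values will nearly coincide, but the default estimate is an odds ratio and the hypothesis is a relative reduction in risk. The trial is unblinded to clinicians and participants, so the choice is best fixed before results are known.

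**Working it through.** **1. The plan's own sample size.** Inputs from Sample size calculations: p1 = 0.38, p2 = 0.25, alpha 0.049 (sidedness not stated, taken as two-sided, z = 1.969), power 90% (z = 1.282). With pooled p = 0.315:

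n = [1.969·√(2·0.315·0.685) + 1.282·√(0.38·0.62 + 0.25·0.75)]² / 0.13² = 268 per group, or 283 with continuity correction.

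The article says the figure was rounded up to 300, and 300 covers both. Power at 300 per group is 93.0% without and 91.7% with the correction. The stated 90% is met by the unadjusted test.

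**2. The two effect scales at the design rates.**
- Risk ratio = 0.25/0.38 = 0.658, a 34% reduction (stated as 35%).
- Odds ratio = (0.25/0.75)/(0.38/0.62) = 0.544, which would look like a 46% reduction if read as a relative risk.

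**3. Cost of leaving parity out.** The article gives neither the parity mix nor parity-specific caesarean rates, so these are assumptions: 60% nulliparous (f = 0.6), a parity odds ratio of 2, 3 or 5, a common treatment odds ratio across strata, and overall rates held at 38% and 25%. With n = 300 per group:

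- Unadjusted SE of the log risk ratio = √[0.62/(300·0.38) + 0.75/(300·0.25)] = 0.1243.
- Correct SE under stratification = √[W_c/(300·0.38²) + W_t/(300·0.25²)], where W = f·q1(1−q1) + (1−f)·q0(1−q0) is the within-stratum variance in the control (c) or lactate (t) arm, and q1 and q0 are the nulliparous and parous rates.
- True alpha of the unadjusted test = 2·[1 − Φ(1.969/k)], with k = √[W_c/(0.38·0.62)], taking both arms at the control rates under the null.

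Worked case, parity odds ratio 3: control rates 0.478 and 0.234, so W_c = 0.6·0.478·0.522 + 0.4·0.234·0.766 = 0.221. Lactate-arm rates are 0.325 and 0.138, so W_t = 0.179. Correct SE = 0.1211; ratio 0.1211/0.1243 = 0.975. k = √(0.2213/0.2356) = 0.969; alpha = 2·[1 − Φ(2.031)] = 0.042.

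| Parity odds ratio | Control rates, nulliparous / parous | Correct ÷ unadjusted SE (log RR) | Unadjusted interval too wide by | True alpha | Power gain from adjusting |
|---|---|---|---|---|---|
| 2 | 44% / 28% | 0.989 | about 1% | 0.046 | 0.3 points |
| 3 | 48% / 23% | 0.975 | about 3% | 0.042 | 0.6 points |
| 5 | 52% / 18% | 0.951 | about 5% | 0.036 | 1.2 points |

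A null simulation with 400,000 replicates gave 0.046, 0.042 and 0.035 for the unadjusted test and 0.049 to 0.050 for the stratified test.

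Over a wider grid (50% to 80% nulliparous, parity odds ratio 1 to 8), the interval is 0% to about 10% too wide, the lowest true alpha is 0.027 and the largest power gain is 1.8 points. If parity is not prognostic, nothing changes.

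**4. The logistic model behaves differently.** In the same three cases, adding parity raises the SE of the log odds ratio from 0.179 to 0.181, 0.184 and 0.189, while the odds ratio moves from 0.544 to 0.536, 0.526 and 0.508. The statement that the interval is too wide therefore applies to the risk ratio and risk difference, not to the log odds ratio.

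**The case against.** The strongest reply is that a reader might infer that the whole primary comparison ignores parity, and the article does not show that. It is silent on the covariates of the logistic model. A natural reason to add a regression for this one endpoint is to adjust, and parity is the obvious candidate. A covariate list is commonly left to a full protocol or analysis plan, and neither is at hand. This stands: omission of parity is established only for the chi-squared test and risk ratio as named.

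A reader might also infer that the conclusion will turn on which of the two tests is quoted. If the logistic model is unadjusted, that is not so. With 114 v 91 caesareans in 300 per group, Pearson chi-squared gives p = 0.0477, logistic Wald 0.0481, likelihood ratio 0.0475 and the log risk ratio 0.0489, all on the same side of 0.049. The tests can diverge materially only if the model has covariates, in which case it may well include parity. The two complaints cannot both hold at full strength.

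Third, the article never mentions an odds ratio. The only effect measure it names is the risk ratio, which is the scale of the hypothesis. The logistic sentence, being specific to caesarean section, can be read as the primary analysis. This also stands: there is an ambiguity, not a contradiction, and the odds ratio is only what logistic regression reports by default.

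Finally, the loss is small, conservative and rests on assumed rates. That limits the importance of the point. It does not remove it, because the article positively chooses an unstratified test and risk ratio after a stratified randomisation, and a better-matched analysis costs nothing.

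**Conclusion.** The point holds as a modest improvement. The chi-squared test and risk ratio do not reflect the stratified randomisation, and the Analysis section leaves open both the role of parity in the logistic model and which analysis is primary.

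The size is conditional on parity being prognostic: risk-ratio intervals about 1% to 5% too wide and true alpha about 0.046 to 0.036, under the assumed 60% nulliparous and parity odds ratios of 2 to 5. The direction is conservative, so type I error is not inflated. The documents do not support reading this as a threat to validity, to the sample size or to the stated 90% power. The scale mismatch, 0.66 against 0.54, follows from the plan's own rates and affects how the result would be reported against the hypothesis.

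**What to change.** In the Analysis section, name one primary analysis of caesarean section: a risk ratio stratified by or adjusted for parity (Mantel-Haenszel, or modified Poisson regression with parity as a covariate), tested at 0.049 with the sidedness stated, and the risk difference alongside. Label the unadjusted chi-squared test and the logistic regression as supportive, and state the covariates of the logistic model.

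The cost is wording only. Parity is known for every randomised woman because it determines the randomisation stratum, no new data are needed, and the sample size stays at 600.

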### Intrapartum lactate values

Observational studies suggest that fetal lactate concentrations are constant during the first stage of labour in the absence of hypoxia, and that intrapartum lactate measurements are better than estimations of pH for the prediction of severe neonatal morbidity [25, 33, 34, 40, 41]. Nordström [42] found that, on average, maternal lactate rose by 2 mmol/l per 30 min in the second stage of labour. Fetal lactate concentrations correlate positively with the duration of active pushing at a rate about half that of the maternal lactate (1 mmol/L per 30 min) [42]. The question of whether this lactate rise is driven by fetal hypoxia or derived from the mother was investigated by studying the arterio-venous lactate difference at birth. They found that the main contributor to the fetal lactate increase is the fetus itself, especially with prolonged second stage [42]. This is also supported by animal studies [43]. These findings suggest that fetal scalp lactate measurements remain an appropriate indicator of fetal hypoxia in second stage, particularly, for example, when the fetal head is relatively high in the mother’s pelvis and a dense epidural analgesia is in place that limits the mother’s ability to bear down and give birth to the baby in a short timeframe (i.e. minutes). The clinical appropriateness of performing a FBSLM in response to abnormal fetal heart rate monitoring in active/advanced second stage warrants consideration, where the option of assisting the birth with vacuum or forceps would be a reasonable option, achievable within minutes, rather than delaying this intervention to take a blood sample.

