### Hypothesis

When a woman in labour has a non-reassuring CTG, she has a 38 % chance of delivery by caesarean section [12]. We hypothesise that the addition of FSBLM will reduce this rate from 38 % to 25 %, which is a 35 % relative reduction.

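### The analysis of caesarean section names no baseline covariate; prespecifying adjustment for cervical dilatation and parity would be a modest, low-cost gain

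*Protocol article*

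**What the plan says.** The Analysis section of the protocol article gives two statements that apply to caesarean section. The general one is "Proportions will be compared by Chi-squared analysis, risk ratios and their 95 % confidence intervals". The specific one is "Logistic regression will compare the between-group difference in caesarean section". Neither is labelled primary. No covariate is named, and nothing says that the logistic model is unadjusted. The analysis set is clear: "Analysis will be by intention to treat and all randomised subjects will be included".

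Under Randomisation and group allocation, women are "randomised in a 1:1 ratio to the CTG-only group or the CTG + lactate group", and the sequence is "stratified for parity (nulliparous, parous"). Parity is the only stratification factor.

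The Inclusion criteria require cervical dilatation of at least 3 cm. They set no upper limit, and the Exclusion criteria do not remove women in second stage. The only text that links stage of labour to mode of birth is in the Background, under Intrapartum lactate values. It describes advanced second stage as a setting "where the option of assisting the birth with vacuum or forceps would be a reasonable option, achievable within minutes".

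**The concern.** Women can enter at any dilatation from 3 cm to full. By the protocol's own reasoning, a quick assisted vaginal birth may be open to a woman in advanced second stage. Dilatation at entry may therefore carry information about whether an operative birth will be a caesarean. It is assessed before allocation, so adjusting for it cannot introduce bias through the treatment. The stratification does not balance it.

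Two things are at stake, both small. Outcome variation that a baseline variable could explain stays unexplained. And if the arms happened to differ visibly in dilatation, the team would have to decide whether to adjust after seeing the data, unless a rule had been written beforehand.

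**Working it through.** **Inputs from the protocol.** Caesarean rates: "We hypothesise that the addition of FSBLM will reduce this rate from 38 % to 25" per cent (Hypothesis). Size: "total 600, alpha 0.049 (to allow for one interim analysis), power 90" per cent, with 300 per group (Sample size calculations). Sidedness is not stated; two-sided is used here, so z = 1.969 for alpha 0.049 and z = 1.282 for 90% power.

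**The plan's own figure.** The pooled proportion is (0.38 + 0.25)/2 = 0.315.

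n per group = [1.969·√(2·0.315·0.685) + 1.282·√(0.38·0.62 + 0.25·0.75)]² / 0.13² = (1.293 + 0.834)² / 0.0169 ≈ 268.

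With continuity correction it is 283. The protocol says its figure was rounded up, so 300 is consistent with either. Power at 300 per group is Φ[(0.13·√300 − 1.293)/0.650] = Φ(1.473) = 93.0%. With continuity correction it is about 91.7%.

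**Effect of adjusting.** The documents give no figure for how dilatation relates to caesarean risk, so a range is assumed. Trials of 600 women were simulated, 4,000 per scenario, with one standardised baseline covariate. Marginal rates were held at 38% and 25%, and alpha at 0.049.

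| Assumed odds ratio per SD | Power unadjusted | Power adjusted | SE of log odds ratio, unadjusted → adjusted | Conditional log odds ratio | Variance of standardised risk difference ÷ unadjusted |
|---|---|---|---|---|---|
| 1.0 | 92.9% | 93.0% | 0.179 → 0.180 | −0.609 | 1.00 |
| 1.25 | 92.8% | 93.1% | 0.179 → 0.181 | −0.615 | 0.99 |
| 1.5 | 93.9% | 94.7% | 0.179 → 0.183 | −0.630 | 0.97 |
| 2.0 | 94.0% | 95.5% | 0.179 → 0.189 | −0.667 | 0.92 |
| 2.5 | 93.2% | 96.1% | 0.179 → 0.195 | −0.707 | 0.86 |
| 3.0 | 92.7% | 96.7% | 0.179 → 0.200 | −0.744 | 0.82 |

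The marginal log odds ratio is ln[(0.25/0.75)/(0.38/0.62)] = −0.609 throughout. True unadjusted power is the same in every row, so the spread in that column is simulation noise: √(0.93·0.07/4000) ≈ 0.4 points.

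On the log-odds scale the standard error rises with adjustment. Power improves because the conditional effect lies further from zero. Precision improves only for the standardised risk difference.

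**A second set of assumptions.** Take three equal dilatation bands averaging 38% in the CTG-only group. The share of outcome variance explained is the between-band variance divided by 0.38·0.62 = 0.2356.

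- Bands 45/38/31%: 0.00327/0.2356 = 0.014. Power 93.4% → 93.5%; risk-difference variance about 1% lower.
- Bands 55/40/19%: 0.0218/0.2356 = 0.093. Power 93.4% → 94.8%; variance about 7% lower.
- Bands 62/40/12%: 0.0419/0.2356 = 0.178. Power 93.4% → 96.4%; variance about 13% lower.

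**Size of chance imbalance under the same bands.** The 95% range for the between-arm difference in expected CTG-only risk is 1.96 · SD of band risk · √(2/300). With SDs of 0.057, 0.148 and 0.205 this gives about ±0.9, ±2.4 and ±3.3 percentage points, against a target difference of 13.

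**The case against.** The strongest objection is that the article is silent on covariates and does not rule them out. A covariate list is commonly left to the full protocol or SAP, neither of which is shown. The unadjusted comparison is already provided by the chi-squared test and risk ratio, so a separate logistic model is quite compatible with planned adjustment. This stands. A reader might infer that the plan fixes an unadjusted primary model and so ignores dilatation, but the text neither says that nor ranks the logistic model above the risk ratio.

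Other stronger readings also fail:

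- **Dilatation strongly governs caesarean risk.** No figure supports this. The Background remark concerns whether to take a scalp sample in advanced second stage. The same paragraph describes second-stage women with a high fetal head and dense epidural, for whom a quick birth is less likely.
- **Its value is known for every woman.** Eligibility needs only the 3 cm threshold. Nothing says that the value at randomisation is recorded.
- **Free precision is thrown away.** This is wrong for the log odds ratio, whose standard error does not fall.
- **Chance imbalance distorts the result.** Imbalance under randomisation is random error, already covered by the confidence interval and the type I error rate. It is not bias.

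Parity, as the stratification factor, also has a firmer documentary claim to be in the model than dilatation. What survives is that naming covariates in advance is legitimate, lost power in no scenario beyond simulation noise, and costs little.

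**Conclusion.** The point holds as an optional improvement. The protocol article names no covariate for caesarean section, although dilatation is assessed before randomisation, is left unbalanced by the parity-only stratification, and is plausibly prognostic.

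The gain is about 0 to 4 power points over roughly 92–93%, and about 0 to 18% less variance for the standardised risk difference. Both ranges rest on an assumed association (odds ratio 1 to 3 per SD), on two-sided alpha of 0.049, and on the planned 38% and 25%. If dilatation is only weakly prognostic, the gain is essentially nil. The unadjusted analysis remains valid, and the planned 90% power does not depend on adjustment.

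**What to change.** First check whether the SAP already names covariates for this endpoint. If it does not, add before unblinding:

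- a logistic model for caesarean section with allocated group, parity (nulliparous, parous) and cervical dilatation at randomisation, either in cm or in prespecified bands such as 3–5 cm, 6–9 cm and full dilatation;
- the risk difference and risk ratio obtained by standardising over that model, with 95% confidence intervals, as the reported effects;
- the unadjusted risk ratio as the supporting analysis.

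The cost is recording the dilatation value at randomisation rather than only the threshold, plus one model term beyond parity. The adjusted odds ratio is conditional on the covariates and differs from the marginal one, which is why the standardised effects should be the ones reported.
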